## Abstract

**Background:**

Laparoscopy training courses have been established in many centers worldwide to ensure adequate skill learning before performing operations on patients. Different training modalities and their combinations have been compared regarding training effects. Multimodality training combines different approaches for optimal training outcome. However, no standards currently exist for the number of trainees assigned per workplace.

**Methods:**

This is a monocentric, open, three-arm randomized controlled trial. The participants are laparoscopically-naive medical students from Heidelberg University. After a standardized introduction to laparoscopic cholecystectomy (LC) with online learning modules, the participants perform a baseline test for basic skills and LC performance on a virtual reality (VR) trainer. A total of 100 students will be randomized into three study arms, in a 2:2:1 ratio. The intervention groups participate individually (Group 1) or in pairs (Group 2) in a standardized and structured multimodality training curriculum. Basic skills are trained on the box and VR trainers. Procedural skills and LC modules are trained on the VR trainer. The control group (Group C) does not receive training between tests. A post-test is performed to reassess basic skills and LC performance on the VR trainer. The performance of a cadaveric porcine LC is then measured as the primary outcome using standardized and validated ratings by blinded experts with the Objective Structured Assessment of Technical Skills. The Global Operative Assessment of Laparoscopic Surgical skills score and the time taken for completion are used as secondary outcome measures as well as the improvement of skills and VR LC performance between baseline and post-test. Cognitive tests and questionnaires are used to identify individual factors that might exert influence on training outcome.

**Discussion:**

This study aims to assess whether workplaces in laparoscopy training courses for beginners should be used by one trainee or two trainees simultaneously, by measuring the impact on operative performance and learning curves. Possible factors of influence, such as the role of observing the training partner, exchange of thoughts, active reflection, model learning, motivation, pauses, and sympathy will be explored in the data analysis. This study will help optimize the efficiency of laparoscopy training courses.

**Trial registration number:**

DRKS00004675

## Background

Minimally invasive surgery (MIS) has been established as a standard for many operations in abdominal surgery. However, in comparison to open surgery, laparoscopic surgeons face technical challenges and increased psychomotor demands resulting in an additional learning curve and prolonged operative times [1-4]. Different training modalities enable prospective surgeons to acquire the psychomotor abilities and surgical skills necessary before applying them to patients [5-9]. Current training modalities include box and pelvi trainers with real surgical instruments, organ models, cadavers, cadaveric organs, live animal models, and computer simulators. Cadavers and animal models provide the most realistic training for operations but are of limited availability [10,11]. Box and pelvi trainers enable the acquisition of basic skills with real instruments and are essential for the training of knot tying and suturing. Virtual reality (VR) trainers enable repetitive training of both basic skills and operations in a virtual environment. In addition, trainees receive automated instructions and feedback, and their performance can be recorded in order to monitor training progress [12,13]. However, at their current level of performance, VR trainers still lack realism in terms of tissue interaction and haptic feedback, and performance feedback is often limited to metric parameters such as the instrument path length [11].

Positive learning effects of both box and VR trainers have been shown for practical laparoscopic skills without clear superiority of one over the other. Other studies have proven positive effects on the duration of operations and on the clinical outcome of both training modalities [5-7,14,15]. When box trainers are augmented with cadaveric organs, surgical interventions can be realistically simulated, e.g., laparoscopic cholecystectomy (LC) [16-18]. Online learning platforms provide videos of operations, explanations, and teaching of surgical techniques, the relevant anatomy, and perioperative management [19,20]. The efficacy of online learning modules has been studied with positive results for online learning both alone and in combination with other training modalities [21]. Multimodality training combines the available training modalities for optimal outcome [11,22,23].

The present study is primarily directed at identifying how many trainees should be assigned per workplace in laparoscopy training courses. One may surmise that the option of having one trainee per workplace would be the optimal training environment and lead to the best training outcome. However, there is currently no evidence available for surgical training [24]. Different factors might exert influence on the outcome of training in pairs or alone. Pairs have many potential advantages, such as the exchange of knowledge, technical discussions between training partners, more pauses with active reflection, analysis of errors, and model learning when the partner trains [25-27]. Evidence from training psychology suggests higher efficiency with pauses and feedback between repetitions of exercises, thus supporting the concept “train less and learn more” [28]. For example, positive effects of intraoperative breaks during long operations have been shown to result in lower stress levels while preserving operation time [29]. Observing peers during learning of practical skills in medical education has been shown to accelerate the learning process, e.g., for physical examination skills [30]. On the other hand, the available literature suggests a learning curve with a certain number of repetitions required for reaching proficiency levels of given tasks and procedures in laparoscopic surgery, thereby suggesting that trainees with a workplace to themselves would benefit [24,31-34]. The secondary objective of this study is to analyze individual and general factors that influence laparoscopic learning curves and test results. The factors assessed include sex, cognitive measures, gaming experience, and personal characteristics [35,36].

## Methods

### Objectives

The primary goal of this study is to examine whether study participants who undergo laparoscopic training individually (group 1) perform better after the training than study participants who undergo the same training in paired teams (group 2). The control group (group C), which does not receive training, exists to assess the importance of training for a successful operative outcome. Baseline and post-tests are performed on the VR trainer (Figure 1). The operative performance in all three groups will be tested on a cadaveric porcine model with the pulsating organ perfusion (POP) trainer at the end of the study and will be evaluated according to standardized and validated assessment criteria by blinded raters [37-40]. Secondary goals include assessing the influence of individual trainee characteristics on surgical training and performance [35,41,42].

**Figure 1 F1:**
[figure not shown]
Study protocol flow chart.

### Study design

This is a registered prospective, single-center, rater-blinded, three-arm, parallel-group randomized controlled trial (DRKS00004675).

### Setting and participants

This study is carried out in the MIS training center of the Department of General, Visceral, and Transplantation Surgery at Heidelberg University Hospital. This study offers voluntary laparoscopic training courses to medical students at Heidelberg University during their clinical years.

### Inclusion and exclusion criteria

Inclusion criteria are students enrolled at Heidelberg University Medical School during their clinical years. Exclusion criteria are students who have already participated in laparoscopy training courses or who have experience assisting in laparoscopic surgeries.

### Introduction to laparoscopic cholecystectomy by online learning

All participants work with online learning modules for two hours as an introduction to LC at the beginning of the study [43]. This is done in a standardized fashion by using the same room at the Department of Surgery at Heidelberg University with identical surrounding conditions in order to rule out any difference between participants. The trainees get assistance with the necessary online registration and are given an explanatory introduction by trained staff in a standardized way to begin the LC module on http://www.webop.de. During this, the trainees are asked to study the anatomy, illustrations, and videos of the procedural techniques. Following this general overview, the participants learn more specific LC information including the operating room set-up and trocar placement. Next, the trainees watch the “*Laparoscopic cholecystectomy: a gold standard case for dissection of Calot’s triangle*” module on http://www.websurg.com to complement what they had previously learned. At the end of the online learning session a standardized multiple choice test is used to check the learning success. The trainees are informed about the multiple choice test at the beginning of the online learning module to ensure that learning motivation is high.

### Introduction to the training modalities in the training center

The participants receive a standardized introduction and instructions on using the box and VR trainer by trained staff. Thus, students can familiarize themselves with the training facilities and training devices prior to the start of the tests and exercises.

### Baseline test

After online learning and a VR introduction, all participants take a baseline test at the VR trainer for an initial assessment of basic skills and LC performance. After this test, participants are randomly assigned to one of the three groups.

### Randomization

Study participants are stratified according to sex and randomly assigned to the training groups or control group in a 2:2:1 ratio by block randomization with a variable block length. Group 1 trains alone, group 2 trains in paired teams, and the control group C receives no training between tests (Figure 1). There are indices for differences between males and females in the acquisition of laparoscopic surgical skills [44,45]. After the participants have finished the baseline test on the VR trainer, an employee of the Department of Surgery at Heidelberg University will perform the randomized distribution of subjects using sealed envelopes. The employee responsible for the randomization and group assignment is otherwise not involved with the training, tests, and data from the present study.

### Training curriculum

The curriculum uses multiple training modalities to ascertain several advantages of each, and to give variety to the trainees for ensuring high motivation. In the present study, the multimodality training embraces online learning, box trainers, and VR training. The training groups participate in a standardized and structured multimodality training curriculum involving box and VR trainers either individually (group 1) or in pairs (group 2). Basic skills are trained with the box (Table 1) and VR trainers (Table 2). Procedural skills and complete LCs are practiced on the VR trainer (Table 3). Training in pairs involves less repetitions of each training task per individual participant since pairs are given the same total training time per workplace and must take turns every 30 minutes. The basic and procedural skills exercises of the curriculum are repeated by the training groups during two training sessions of 4 hours until training time is over. The remaining 4-hour training session is used to repeat the LC modules on the VR trainer. The VR trainer permanently records data from exercises including time, precision, economy of motion, instrumental distance, and the number of misaligned clips.

**Table 1 T1:** Box-trainer basic skills exercises

**Nr.**	**Exercise**
1	Moving matches from a box passing them to the other instrument
2	Crossing of 6 rubber bands in a device of 6 screws
3	Cutting out a predefined circle on paper
4	Drawing a rubber band in a device consisting of eyelets and hooks
5	Cutting out a predefined triangle located on a rubber glove
6	Leading needle and thread in the correct order through eyelets screwed on a board
7	Closing a 5 cm cut on foam with a running suture
8	Attaching a simple interrupted stitch on foam

**Table 2 T2:** VR trainer basic skills exercises

**Basic skill**	**Exercise**
Camera manipulation	The 0° and a 30° angled camera is used to locate 10 balls and snap photos of them
Eye-hand coordination	Objects of blue or red colour have to be touched with the respectively colored instrument tips
Clip-application	Ducts have to be clipped to stop the leakage
Clipping/grasping	Leaking ducts need to be safely grasped and then clipped
Two-handed maneuvers	Balls have to be grasped from a jelly mass and placed into a bag with both instruments
Circular cutting	A circular form has to be freed from tissue attachments by cutting with scissors while retracting the form
Electrocautery	Highlighted tissue bands have to be dissected applying hook cautery

**Table 3 T3:** VR trainer procedural skills exercises for laparoscopic cholecystectomy

**Procedural skill**	**Exercise**
Clipping and cutting	The gallbladder is already exposed with Hartmann’s pouch retracted laterally by a static tool. The cystic duct and artery have to be clipped and cut. Instructions are given.
Exposure of Calot’s triangle	The gallbladder has to be grasped to expose Calot’s triangle. With correct exposure the students are instructed to clip the cystic duct and artery with the second instrument.
Dissection of cystic duct and artery	The gallbladder’s infundibulum has to be retracted for safe dissection of the highlighted cystic duct and artery to achieve the critical view of safety.
Gallbladder separation	The gallbladder is to be separated from the liver bed with eletrocautery. The line of dissection becomes highlighted with adequate retraction.

### Post-test

The post-test includes the basic skills and LC modules on the VR trainer and a porcine cadaveric LC. The groups 1 and 2 take the VR trainer post-test at the end of the training curriculum and the porcine cadaveric LC test on the POP trainer is taken on a separate day.

### Control group

Group C does not participate in the repetitive training exercises, but is provided the same E-learning, LC introduction, and tests as the training groups. Group C takes the VR baseline test on the first day of the study. The post-test on the VR and POP trainer LC are taken on a separate day.

### Blinded test evaluation

The post-test LC with the POP trainer and cadaveric animal organ is used to evaluate and compare the operative performance of all participants. The POP trainer simulates MIS with perfused cadaveric organs. The artery of a hepato-biliary organ can be catheterized and linked to the frequency and pressure controlled POP trainer pump and perfused by colored water. The perfused liquid flows back into the POP trainer via side arms of the arteries, veins, and parenchymal lesions. The Objective Structured Assessment of Technical Skills (OSATS, range 20 to 100) is used as the primary endpoint of the study (Table 4). The expert raters are blinded to the training status of the participants. The OSATS consists of two evaluative spectra and allows for the evaluation of general laparoscopic surgical skills as well as specific procedural and technical skills for the operation. The unweighted sum of the two scales will be evaluated as the primary endpoint.

**Table 4 T4:** Objective structured assessment of technical skills (OSATS) scores

**OSATS**	**Objective structured assessment of technical skills**	**20–100 points**
**GRS**	**General rating scale**	**6–30 points**
	Respect for tissue	1–5 points each
	Time and movement	
	Use and knowledge of instruments	
	Use of camera-assistance	
	Operational duct and anticipation	
	Need of assistance	
**STS**	**Specific technical skills scale**	**14–70 points**
	Retraction of the gallbladder and exposition of Calot’s triangle	1–5 points each
	Preparation of the cystic duct	
	Clipping and sectioning of the cystic duct	
	Preparation of the cystic artery	
	Preparation of the liver bed	
	Specific knowledge about operational techniques	
	Overall quality of the operation	

With the general rating scale (GRS), the rater evaluates the trainee in the following categories (1 to 5 points each): respect for tissue, time and movement, use of instruments, knowledge of instruments, use of camera-assistance, operational duct and anticipation, and need of assistance in general. The GRS covers a range from 6 (minimum) to 30 points (maximum). The specific technical skills scale (STS) measures the retraction of the gallbladder and exposition of Calot’s triangle, preparation of the cystic duct, clipping and sectioning of the cystic duct, preparation of the cystic artery, preparation of the liver bed, specific knowledge about operational techniques, and the overall quality of the operation [38,46]. In this study, the STS scale is applied in a modified way due to specific circumstances: as the criteria “incision and insertion of the port” and “extraction of the gallbladder” refer to surgeries performed on humans or on living animals and cannot be rated properly on the POP trainer, both are replaced by the criteria “knowledge of surgery specific aspects” and “quality of the operative outcome”. The STS covers a range from 14 (minimum) to 70 points (maximum).

In addition to the OSATS criteria, the rater will use the Global Operative Assessment of Laparoscopic Surgical Skills (GOALS, range 6 to 30) score and the time required to perform the operation as secondary endpoints (Table 5) [40]. The given time to finish the LC is 80 minutes so as to ensure the feasibility of this study. Previous studies have shown that 80 minutes is sufficient to assess the competence of each participant for all major parts of the operation.

**Table 5 T5:** Global operative assessment of laparoscopic skills – GOALS score

**GOALS – Global operative assessment of laparoscopic skills**	**6–30 points**
Depth perception	1–5 points each
Bimanual dexterity	
Efficiency	
Tissue handling	
Autonomy	
Level of difficulty	

### Primary outcome measure

The primary outcome measure is the operative performance of the study participants during the porcine cadaveric LC on the POP trainer based on the standardized and validated OSATS score.

### Secondary endpoints

The GRS and STS scales of the OSATS score will be evaluated separately as secondary endpoints, as well as the GOALS scores, operative times, and improvement from baseline to post-test on the VR trainer. In all groups, data from the practical exercises will be collected continuously for each participant based on the multimodal standardized training curriculum designed by the Department of Surgery at Heidelberg University. Each individual exercise on the box trainer will be recorded with respect to time and error. The VR trainer software allows for the continuous recording of various parameters for every participant. Based on this recorded data, learning curves can be displayed for all participants and their differences can be analyzed between groups.

Psychometric and personal parameters will be collected for each participant using anonymous questionnaires. The questions will relate to prior laparoscopic experience and leisure behavior with regards to physical activity, computer games, music, and personal interests. Other parameters, e.g., personality traits and spatial awareness, will also be recorded. Group 2 will receive an additional question concerning team training. In addition, participants will evaluate the training methods through a questionnaire. Explorative analyses will be performed using the collected data and possible relations to the training results [42,47].

### Statistical analysis

The normal distribution provides a fairly exact approximation of the distribution of the scale-specific scores (Figures 1 and two in [46]), which allows standard parametric tests to be used to compare the mean OSATS scores of the three groups [46]. In the first step, overall training effects will be analyzed by a linear mixed model with the main effects Group (1, 2, C), gender (stratification factor), and training pair as a random factor nested in Group 2. If the group effect is not significant at α = 5% in this gatekeeper analysis, statistical inference will stop concluding that there is no substantial training effect at all. If the test is significant, all possible pairs of interventions will be compared (1 vs. C, 2 vs. C, 2 vs. 1) in a similar linear mixed model with group, gender, and training pair (if applicable). These latter analyses will be performed at α = 5% two-tailed, without correction for multiplicity (closed test procedure).

Statistical analysis will be based on the intention-to-treat population that includes all participants that have been randomized and have attended at least one training session. Multiple imputation will be used for missing endpoint information, with linear regression of OSATS scores by the baseline performance on the VR trainer.

Sensitivity analyses will be made using mixed best (Group C) and worst-case (Groups 1 and 2) imputation for the three treatment groups, and vice versa, as well as for the per protocol set of participants that attended all trainings and have complete primary endpoint information.

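### The OSATS models leave out the pre-randomisation VR baseline that every participant has: a cheap gain in precision is missed, of a size that depends on an unstated correlation

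*Protocol article*

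**What the plan says.** The article lists the terms of the primary analysis explicitly. Under Statistical analysis, the gatekeeper is a linear mixed model with "main effects Group (1, 2, C), gender (stratification factor), and training pair as a random factor nested in Group 2". If it is significant, the three pairwise comparisons follow "in a similar linear mixed model with group, gender, and training pair (if applicable"), each at two-sided 5%. No baseline performance measure appears in either model.

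Such a measure exists. Under Baseline test, "all participants take a baseline test at the VR trainer for an initial assessment of basic skills and LC performance", and "After this test, participants are randomly assigned to one of the three groups".

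For the primary endpoint the VR baseline has one stated use: missing OSATS scores are multiply imputed "with linear regression of OSATS scores by the baseline performance on the VR trainer". Otherwise it serves a secondary endpoint, "improvement from baseline to post-test on the VR trainer" (Secondary endpoints).

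No single VR baseline score is defined. Under Training curriculum, the trainer is said to record "time, precision, economy of motion, instrumental distance, and the number of misaligned clips".

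**The concern.** A covariate measured before randomisation in everyone can be added to a randomised comparison without risk of bias. If it predicts the outcome, it removes variance from the residual and corrects the estimate for chance imbalance in that covariate. The plan treats the VR baseline as informative about OSATS when a score is missing, but makes no use of it when the score is observed.

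The design has little reserve. Its power for the main comparison, group 1 against group 2, is almost exactly 80%, and the stated calculation contains no term for correlation within training pairs although the model does. At stake are the width of the interval for that comparison and the protection against a chance difference in starting skill, since randomisation is stratified only by sex and the control arm has only 20 participants.

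**Working it through.** **Inputs.** From Sample size determination: 40 per active arm, SD of total OSATS 7.86, difference 5 points, two-sided α = 0.05, stated power 80%. From the Abstract: 100 participants in a 2:2:1 ratio, so 40/40/20. Not in the documents, hence assumed over a range: r, the within-group correlation of the VR baseline summary with OSATS.

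**The plan's own figure.** Standardised effect = 5/7.86 = 0.636. Noncentrality = 0.636/√(1/40 + 1/40) = 2.845. With 77 degrees of freedom (80 less intercept, group and sex), two-sided noncentral t power is 80.2%. The stated 80% is reproduced.

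**With the baseline as covariate.** Three things change:
- Residual SD becomes 7.86 × √(1 − r²).
- One degree of freedom is spent, leaving 76.
- The variance of the group difference is inflated by about 1 + 1/75 for chance imbalance in the covariate.

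Noncentrality = 5 / [7.86 × √(1 − r²) × √(2/40) × √(76/75)].

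| r | Residual SD | Variance ratio (1 − r²)(76/75) | Power for 5 points | Difference detectable at 80% |
|---|---|---|---|---|
| 0 | 7.86 | 1.013 | 79.7% | 5.02 |
| 0.1 | 7.82 | 1.003 | 80.1% | 5.00 |
| 0.2 | 7.70 | 0.973 | 81.3% | 4.92 |
| 0.3 | 7.50 | 0.922 | 83.3% | 4.79 |
| 0.5 | 6.81 | 0.760 | 89.6% | 4.35 |

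The last power is 89.65% before rounding, so a marginally different imbalance factor gives 89.7%.

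**Break-even.** Setting (1 − r²)(76/75) = 1 gives r² = 1/76, so r is about 0.11. Below that the covariate costs slightly more than it returns. The largest loss is at r = 0: 80.2% − 79.7% = 0.5 percentage points.

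**Equivalent sample size.** 40 divided by the variance ratio: 40/0.922 = 43.4 per arm at r = 0.3, and 40/0.760 = 52.6 at r = 0.5.

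**With pairing.** Assume a within-pair correlation of 0.2, also not in the documents. The variance of the group 2 mean then rises by a factor 1.2. Counting 20 pairs and 40 individuals as 60 units leaves 57 degrees of freedom unadjusted and 56 adjusted. Power is 76.0% unadjusted. Adjusted, it is:
- 75.4% at r = 0;
- 78.9% to 79.3% at r = 0.3;
- 85.4% to 86.4% at r = 0.5.

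The lower figures hold the pair variance fixed, as when it arises from shared training. The upper ones let it shrink with the residual.

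**Chance imbalance.** A baseline imbalance of two standard errors is 2√(1/40 + 1/40) = 0.447 SD for 40 vs 40, and 2√(1/40 + 1/20) = 0.548 SD for 40 vs 20. The unadjusted OSATS difference shifts by r × 7.86 × imbalance. That is 1.1 points (r = 0.3) to 1.8 points (r = 0.5) for 40 vs 40, and 1.3 to 2.2 points for 40 vs 20.

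**The case against.** The strongest defence is that nothing here is an error. The model is prespecified, includes the stratification factor and accounts for pairs. Omitting a covariate from a randomised linear comparison neither biases the estimate nor inflates type I error, and chance imbalance is already reflected in the standard error. The stated power belongs to the analysis without the baseline, and it reproduces. All of this stands.

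The defence also says that r may be low. The baseline is a novice's first attempt on a VR trainer. The outcome is an expert-rated cadaveric operation on a different device, after training in the active arms. The Background itself notes the limited realism of VR trainers. This stands too: it is not a baseline of the same measure, and at r = 0.1 there is no gain. Using the baseline for imputation does not show that it predicts strongly, since an auxiliary variable may legitimately appear only in the imputation model.

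A reader might go further and infer that the trial is underpowered or its comparison biased, that starting aptitude is a major source of OSATS variance, or that adjustment would be free. The documents support none of these. They give no correlation, and the adjustment has a small cost. A reader might also take the VR improvement endpoint to be a comparison of raw change scores. Secondary endpoints names the endpoint but fixes no analysis for it, and a baseline-adjusted analysis is compatible with that name.

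What the defence does not remove is the asymmetry: at most about half a point of power lost, against about 3 points gained at r = 0.3 and 9 at r = 0.5. Nor is this a detail left to an unseen analysis plan, because the article states the model terms.

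**Conclusion.** The point holds as a missed efficiency. The gatekeeper and pairwise models omit a pre-randomisation measurement available for every participant, one the plan already relies on for imputation. Validity and the stated 80% power are unaffected.

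The size of the gain is unknown. It is nil or slightly negative below r of about 0.11, about 1 percentage point of power at r = 0.2, and more at higher values. These figures rest on the plan's SD of 7.86, on independent participants except where pairing is shown, and on a linear relation between the baseline summary and OSATS. The change is worth making because its downside is small and bounded, not because a large benefit has been shown.

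**What to change.** Under Statistical analysis, add one VR baseline LC performance summary as a fixed covariate in the gatekeeper model and in all three pairwise mixed models, keeping group, gender and training pair as they are. Name that summary before any unblinded analysis, because the trainer records several metrics and the choice determines r. Use the same summary in the imputation regression, so that the imputation and analysis models agree.

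The cost is one or two sentences, one degree of freedom, at most about 0.5 percentage points of power, and the need to settle on a single score in advance. No new data are needed, and the sample size statement can stay as it is.

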### Sample size determination

We plan to examine 40 study participants in the two active arms. This sample size, together with a two-sided α = 0.05, gives 80% power to detect a standardized effect of d = 0.64 with a power of 80%. This effect represents approximately 2.5 points for the general skills scale and approximately 3.5 points for the specific skills scale. As the parameters of the general skills scale range from 1 to 5 and those for the specific skills from 2 to 10, the aforementioned effect would reflect an improvement of exactly one scale unit, which is fairly small. The determination of the sample size for the total scores of general and specific scales can only be estimated, as the correlation between the two scales is unknown. Assuming a positive correlation of *ρ* = 0.5, the standard deviation for the total scores of the scales would be 7.86 for both groups. With the sample size of 40 participants per group and α = 0.05 two-tailed, a difference of 5 points would be detected (for example 3 points for general skills area and 2 points for specific skills area) with a power of 80%. Even smaller differences can be neglected.

In the other analyses, the active study arms are compared with the control group, which consists of students who do not take part in any laparoscopic training. The effect of this control group would be larger than the one of the previous case, thereby allowing for a significantly smaller sample size. In each comparison, a standardized effect of d = 0.79 with 80% power can be measured, which would represent a mean difference of about 6 points on the OSATS scale (for example 3 points for general skills area and 3 points for specific skills area).

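### A non-significant three-group gatekeeper is to be reported as absence of a training effect, although the gate misses a true effect of the trial's own target size in about 20 to 23% of trials

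*Protocol article*

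**What the plan says.** The Objectives section puts one comparison first: "The primary goal of this study is to examine whether study participants who undergo laparoscopic training individually (group 1) perform better after the training" than those trained in pairs (group 2). The control group is there to show how much training matters.

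The Statistical analysis section starts with a linear mixed model that tests for any difference among groups 1, 2 and C. The stopping rule reads "If the group effect is not significant at α = 5% in this gatekeeper analysis", then "statistical inference will stop concluding that there is no substantial training effect at all". Only after a significant result are 1 vs. C, 2 vs. C and 2 vs. 1 tested, each at two-sided 5% without adjustment, as a closed test procedure.

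The Sample size determination section gives power for pairwise comparisons only. It states 80% for 1 vs. 2 with 40 per arm (d = 0.64; 5 points at SD 7.86). For the training arms against control it says "In each comparison, a standardized effect of d = 0.79 with 80% power can be measured", which it equates to about 6 points. It gives neither the power of the gate nor an equivalence margin. It expects the effect against control to be larger than the effect between the two training formats.

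**The concern.** A non-significant test says that the data have not shown a difference. It does not say that there is none, or none of a size that matters. To conclude that, a plan needs a margin and an interval that lies inside it, and this plan gives neither. The gate also asks whether any of three means differ, on 2 degrees of freedom. It is not a direct test of training against no training, yet the sentence draws its conclusion about training.

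The conclusion is fixed in advance, so an analyst who follows the plan faithfully must write it. At stake is a published statement that training has no substantial effect in a trial whose data may be compatible with the full effect it was designed to find. The same rule stands before the comparison named as the primary goal, and the stated powers do not mention it.

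**Working it through.** **Inputs from the article.** Allocation: "A total of 100 students will be randomized into three study arms, in a 2:2:1 ratio", hence 40/40/20. SD of the total OSATS score 7.86 (variance 61.78). Target for 1 vs. 2: 5 points. Target against control: about 6 points, or d = 0.79, which is 0.79 × 7.86 = 6.2 points. α = 0.05 two-sided.

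**Assumptions.** Independent observations and no gender effect. The article gives no within-pair correlation; a range is shown below.

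**1. The plan's own figures.** Two-sample t-test, noncentrality d / √(1/n₁ + 1/n₂).
- 1 vs. 2, d = 0.64: 0.64 / √(1/40 + 1/40) = 2.86, power 80.7%. For 5 points, d = 5/7.86 = 0.636, power 80.2%.
- Training arm vs. C, d = 0.79: 0.79 / √(1/40 + 1/20) = 2.88, power 81.0%. For exactly 6 points, d = 0.763, power 78.3%.

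The stated 80% is therefore reproduced, as pairwise power without the gate.

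**2. Power of the gate.** F-test on 2 and 97 df, critical value 3.09, noncentrality λ = Σ nᵢ(μᵢ − μ̄)² / 61.78, where μ̄ is the mean weighted by group size.
- Both formats 6 points above C: μ̄ = (40×6 + 40×6)/100 = 4.8. λ = (80×1.2² + 20×4.8²)/61.78 = 576/61.78 = 9.32. Power 77%, so the gate fails in 23%.
- Both formats 6.2 points above C: λ = 9.32 × (6.2/6)² = 9.96. Power 80%, so it fails in 20%.
- With a within-pair correlation of 0.5 (assumed; variance of the group 2 mean inflated by 1.5, F on 2 and 75 df), the 6-point case fails in about 25%.

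**3. What a narrow miss would look like.** Suppose both trained groups are observed 4.8 points above C, with SD 7.86. Then F = (16 × 4.8²)/(2 × 61.78) = 2.98, below 3.09, and the gate fails. The 95% interval for the pooled difference is 4.8 ± 1.985 × 7.86 × √(1/80 + 1/20) = 4.8 ± 3.9, or 0.9 to 8.7. It excludes zero and contains the 6-point target. The plan would report no substantial effect.

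**4. Effect of the gate on 1 vs. 2.** True difference 5 points, 60,000 simulated trials per row. Without the gate, power is about 80% throughout.

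| True position of control | Gate fails | 1 vs. 2 significant through the gate |
|---|---|---|
| Midway between groups 1 and 2 | 29% | 70% |
| Equal to group 2 | 21% | 74% |
| 1 point below group 2 | 15% | 77% |
| 3.5 points below group 2 | 3.4% | 80% |
| 6 points below group 2 | 0.3% | 80% |

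**5. Effect of the gate on the control comparisons at d = 0.79.** If both formats are 6.2 points above C, 1 vs. C is significant through the gate in about 75%, against about 81% without it. If group 1 is a further 5 points better (means 11.2, 6.2 and 0), 2 vs. C is significant in about 81% either way.

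**6. Error control.** Under the global null, the probability of any false claim is 5.0% with the gate and about 12% for three ungated tests. If 1 vs. 2 is tested outside the gate, it is about 7.6%.

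**The case against.** The strongest reply is that the gate is sound and the fault is one loose phrase. That largely stands. For three groups, an omnibus test followed by unadjusted pairwise tests is a valid closed procedure and holds the familywise error at 5%. A 20% failure rate at d = 0.79 is the ordinary type II error of a test with 80% power. It is also fair that a rule to stop inference does not forbid reporting estimates, and that interval reporting may be set out in a fuller document that is not shown. None of this rescues the sentence itself, which states what is to be concluded.

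A reader might infer three stronger points that the document does not support.

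- *Target effects would be missed in about 40% of trials.* The gate does fail in 39.5% if both formats are 5 points above control. But 5 points is the target for 1 vs. 2; the target against control is about 6.
- *The gate undermines the primary comparison.* The marked losses need paired training to be no better than no training, or worse. The plan expects the opposite: effects against control larger than the effect between formats.
- *The power against control should be restated as 72 to 75%.* That range fits cases in which group 2 gains as much as group 1 (75%) or half as much (72%). It is not general, as step 5 shows, and the stated 80% is correct as pairwise power.

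**Conclusion.** The concern holds for the pre-specified conclusion. Followed as written, the plan would report no training effect in about 20 to 23% of trials in which both formats truly reach the target advantage over control, and in up to about 25% with a within-pair correlation of 0.5. These figures rest on 40/40/20, SD 7.86, no gender effect and, for the 20 to 23%, independent observations.

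The order of testing is not an error. The loss of power for 1 vs. 2 is at most about 10 percentage points, arises when control is close to or above paired training, and is essentially nil once control is 3 or more points below it. The stated 80% figures are right for what they describe, but the article does not say that they leave out the gate.

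**What to change.** In Statistical analysis, replace the stopping sentence by:

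> If the gatekeeper is not significant, no group difference is claimed and the result is inconclusive; all three group differences (1 vs. 2, 1 vs. C, 2 vs. C) are reported with 95% confidence intervals whatever the gate shows.

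In Sample size determination, add that the 80% figures are pairwise powers that do not allow for the gate, and that power through the gate depends on the third group's mean. Two examples suffice: about 75% for 1 vs. C at d = 0.79 if both formats benefit equally, and about 81% for 2 vs. C if group 1 is a further 5 points better.

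Both changes are wording only. They leave sample size, data collection and error control as they are.

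Testing 1 vs. 2 outside the gate is an option, not a correction. It would match the stated primary goal and restore the full pairwise power, but it raises the familywise error under the global null from 5% to about 7.6%. If the sponsor chooses it, the plan should state that trade-off.
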